### Statistical analysis and power calculations

The primary null hypothesis is that the total ablation time needed for complete LAVA elimination (ie, primary efficacy metric) will not be different between the 2 study arms. This hypothesis will be tested using a 2-sample *t* test.

PFA lesion delivery time will be, by design, shorter (3 2.5-second pulse trains = 7.5 seconds per ablation site) than RFA (at least 30 seconds per lesion). Furthermore, effective RFA lesion dimensions may vary widely depending on the distribution of myocardial scar, whereas PFA lesions are expected to be more consistent.^25^^,^^38^ Therefore, we envisage the time needed to eliminate targeted LAVAs to differ by at least 50% between the 2 study arms. With a desired power of 80% and a significance level of 0.05, the predicted minimum enrollment is 36 patients (18 in each study arm). This will be increased to 40 patients to allow for a 10% withdrawal rate. 10 additional patients will be screened to allow for possible screen failures.

The secondary efficacy and both primary and secondary safety endpoints will be analyzed using *t* test, rank sum test, or Fisher’s exact test, as appropriate. Time-dependent outcomes will be analyzed as landmark events. However, if the event rates and/or dropout rates are high in either group (≥20%), time-to-event methodology will be adopted (Cox regression and Fine-Gray competing risk models, as appropriate). Univariate and multivariable models will be used.

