**Results:**

40 individuals will be randomized. The primary efficacy metric will be the ablation time needed to eliminate late abnormal ventricular activities in each patient. Additional efficacy and safety endpoints will be interrogated after the procedure and during outpatient follow-up.

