**Conclusion:**

This is the first pilot randomized controlled trial comparing the safety and efficacy of focal PFA vs RFA VT ablation in ICM. Its results will inform the design of future larger studies that will further establish the clinical utility of PFA in the context of scar-related VT ablation.

Key Findings
▪ASCEND-VT is a pilot trial that randomizes patients with ischemic cardiomyopathy and ventricular tachycardia to endocardial ablation using standard radiofrequency vs novel pulsed field ablation catheter.▪The intervention arm will use the new FARAPOINT focal pulsed field ablation catheter (under the US Food and Drug Administration’s investigational device exemption).▪The immediate procedural endpoint in all patients will be total elimination of abnormal electrograms, specifically late abnormal ventricular activity (LAVA).▪The trial’s primary efficacy metric is the time needed to eliminate LAVAs in the 2 study arms. This will be tested for noninferiority.▪Additional efficacy and safety metrics will be assessed after the ablation and over the course of a 6-month follow-up period.

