### Ablation procedure: Substrate ablation

All LAVA areas will be targeted for ablation unless concern for collateral damage is thought to outweigh the benefits by the operator (eg, vicinity of conduction system). Ablation should not be performed in the proximity of metallic devices (such as intracardiac lead electrodes) to avoid arcing, cardiac trauma, and/or damage to the devices.

In the control arm, ablation will be done using commercially available contemporary RFA contact force–sensing slow-flow irrigated RFA catheters using standard irrigation settings and 30–50 W output for at least 30 seconds. The goal of each lesion will be the complete elimination of LAVA and/or local myocardial noncapture during high-output pacing (10 mA/2 ms to 20 mA/2 ms).

In the intervention arm, PFA will be done via the FARAPOINT focal catheter (Boston Scientific) using 5 bipolar/biphasic trains of 2.0 kV applications delivered over 2.5 seconds; the number of applications will be repeated based on lesion depth needs. There will be no limit on the number of RFA or PFA lesions.

In both study arms, the ablated areas will be remapped using the same catheter used for baseline substrate mapping and elimination of LAVAs will be confirmed by the primary operator (post hoc data review by the principal investigators [[name] and [name]] to confirm LAVA elimination will also be performed, and any discrepancies will be documented). In addition, high-output pacing (10 mA/2 ms to 20 mA/2 ms) will be delivered to the ablated sites to confirm noncapture at high or very high output. If persistent LAVAs and/or locations with persistent myocardial capture are identified, additional ablation is encouraged in both study arms.

Patients with an anticipated need for epicardial access will be excluded from the study. However, in cases where ad hoc epicardial access becomes necessary in an enrolled study subject (eg, unexpected identification of an epicardial VT focus during the procedure), epicardial mapping/ablation can be performed as clinically necessary; however, only RFA ablation is permitted in the pericardial space (or inside the coronary sinus system).

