### Endpoints

The efficacy and safety endpoints are presented in Table 3. In brief, the primary efficacy endpoint is the total time needed to ablate and eliminate all targeted LAVAs. The secondary efficacy endpoints include other procedural metrics (including postprocedural inducibility, total procedural duration, and fluid balance) and time-dependent outcome metrics such as total mortality, hospital admissions for cardiovascular indication, and recurrences of VT/ventricular fibrillation. Safety endpoints include a range of possible periprocedural complications, with particular attention paid to issues that may be more relevant to PFA; this includes any coronary events (including coronary vasospasm), acute kidney injury, and changes in LVEF and/or evidence of new wall motion abnormalities.

**Table 3 tbl3:** Efficacy and safety endpoints

Primary efficacy endpoint	Objective/rationale
Time needed to eliminate LAVAs	This is the primary procedural efficacy metric highlighting a key potential advantage of PFA over RFA technology.
Acute secondary efficacy endpoints	Objective/rationale
Total procedural duration	These are additional procedural efficacy metrics expected to mirror the primary efficacy endpoint.
Total fluid administered by the ablation catheter	
Total fluid administered during the procedure	
Fluid balance at the end of the procedure	
Ongoing presence of LAVAs at the end of the procedure	A different efficacy metric. LAVA elimination may not always be possible with RFA and is likely always feasible with PFA, although the durability of this elimination remains to be determined.
VT noninducibility at the end of the procedure	A standard acute endpoint metric, although its utility has lately been challenged^45^
Time-dependent secondary efficacy endpoints (assessed 6 mo postoperatively)	Objective/rationale
Recurrences of sustained VT leading to appropriate ICD interventions (ATP or shock) or any symptomatic sustained VT	Standard clinical follow-up endpoints. The ASCEND-VT trial is not powered to show significant differences in these outcomes. However, if major differences are ultimately observed in these metrics, future studies will have to elucidate whether the procedural workflow of PFA needs to be adjusted.
Any documented sustained VT below the detection rate of the ICD	
All-cause mortality	
VT burden (number of appropriate ICD therapies in the 6 mo before ablation vs 6 mo after the ablation)	
Hospital admissions for cardiovascular causes	

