The limitations of the ASCEND-VT trial primarily stem from the study’s relatively small size. As discussed earlier, the trial is not powered to detect differences in clinical outcomes (such as VT recurrences or mortality) between the 2 study arms. Similarly, the study may not be able to estimate the relative risk of PFA for presumably uncommon complications (eg, stroke). Furthermore, the trial is not designed to confirm the durability of LAVA elimination; this may be particularly relevant in the PFA arm where local electrogram elimination may be reversible in some cases. In addition, the ASCEND-VT trial will use different mapping systems and mapping catheters in each arm—a logistical constraint stemming from each mapping system’s compatibility with the used ablation catheters. This heterogeneity in the mapping apparatus may inadvertently result in the designation of slightly different ablation targets in each study arm. An analysis will be undertaken wherein the time needed to eliminate LAVA will be normalized to the total surface area exhibiting LAVA at baseline. This additional analysis would generate results independent of the used mapping system and may be a more objective metric of substrate ablation efficiency.

Although the primary study endpoint is elimination of all LAVAs, induction and mapping of VTs when feasible are also allowed to ensure targeting more rare subtypes of non–scar-related VTs. Given the randomized nature of this study, this would not be expected to substantially affect the primary study endpoint.

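### The tested primary variable, ablation time to complete LAVA elimination, has no value for patients with residual LAVAs, whom the article expects mainly in the RFA arm

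*Protocol article*

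**What the plan says.** The article words its primary variable in several places.

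- **Statistical analysis and power calculations, hypothesis:** "the total ablation time needed for complete LAVA elimination (ie, primary efficacy metric"). This is compared between arms with a two-sample t test.
- **Same section, power sentence:** "we envisage the time needed to eliminate targeted LAVAs to differ by at least 50" per cent.
- **Endpoints:** "the primary efficacy endpoint is the total time needed to ablate and eliminate all targeted LAVAs".
- **Abstract, Results:** "The primary efficacy metric will be the ablation time needed to eliminate late abnormal ventricular activities in each patient". This says nothing on complete versus targeted.

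Three other parts bear on what these wordings mean in practice.

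- **Ablation procedure: Substrate ablation**, on what the operator treats: "All LAVA areas will be targeted for ablation unless concern for collateral damage is thought to outweigh the benefits by the operator". The example given is closeness to the conduction system.
- **Introduction and Discussion:** both say that with RFA full elimination is sometimes not reached; the Introduction puts this at a substantial share of patients.
- **Table 3:** residual LAVAs at the end of the procedure are an acute secondary endpoint. The rationale given is that RFA may not always eliminate LAVAs, while PFA probably always can.

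**The concern.** A t test needs one number per patient. A time needed to reach complete elimination exists only for patients who reach it. The article itself describes two routes by which a patient does not: the operator spares some LAVAs for safety, or some targeted LAVAs persist despite ablation. It expects the second route mainly in the RFA arm.

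An analyst who follows the hypothesis sentence literally must either leave these patients out or give them a value by a rule that the article does not state. Leaving them out would condition the primary comparison on success after randomization, and more often in one arm than in the other. The arms would then no longer be the randomized groups. The Discussion wants the trial to inform a larger head-to-head study, so the effect size should belong to one quantity that every treated patient has.

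**Working it through.** **1. The plan's own figure.** Inflation for withdrawal: 36 / (1 − 0.10) = 40, as stated. The 36 cannot be derived independently, because the article gives no standard deviation. Solved backwards, 18 per arm with 80% power at two-sided 0.05 (two-sided is assumed) implies a standardized difference d = 0.961. For a 50% difference that is a common SD of 0.50 / 0.961 = 0.52 of the control mean. This is an implied value and not a stated one.

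**2. Which patients have a value.** By type of patient after the procedure:

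| Patient | Time to complete elimination | Time to eliminate targeted LAVAs | Ablation time applied to targeted LAVAs |
|---|---|---|---|
| All LAVAs targeted, all gone | yes | yes | yes |
| Some spared, all targeted ones gone | none | yes | yes |
| All targeted, some persist | none | none | yes |
| Some spared, some targeted ones persist | none | none | yes |

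The hypothesis sentence is the first column of times. The power sentence and the Endpoints section are the second. Going from the first to the second rescues only the second row. The patients whom the Introduction, Table 3 and Discussion describe, with LAVAs that RFA fails to eliminate, are in the last two rows and lack a value under both existing wordings. Only the third column covers everyone.

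**3. Size of the power loss, for illustration.** The article gives no rate of incomplete elimination, so the counts are assumptions. Hold d at 0.961 with 18 PFA patients, and suppose that 2, 4 or 6 of 18 RFA patients have no value:

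- RFA n = 16: power 0.774
- RFA n = 14: power 0.742
- RFA n = 12: power 0.702

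These figures apply to residual LAVAs of either cause under the complete wording. They do not measure the difference between the two wordings, because no split between spared and resistant LAVAs is given.

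**4. Size of the bias, for illustration.** As an extreme, assume normal times with RFA mean 1.00, PFA mean 0.50 and SD 0.52, and let the patients left out be exactly the longest RFA cases. With a fraction p removed, the RFA mean becomes 1 − 0.52 × φ(z)/(1 − p), where z is the normal quantile at 1 − p.

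- p = 2/18: 1 − 0.52 × 0.213 = 0.889; apparent reduction 1 − 0.50/0.889 = 44%
- p = 4/18: 1 − 0.52 × 0.383 = 0.801; apparent reduction 1 − 0.50/0.801 = 38%
- p = 6/18: 1 − 0.52 × 0.545 = 0.716; apparent reduction 1 − 0.50/0.716 = 30%

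A true 50% reduction would thus appear as 30% to 44%. The real shift would be smaller if incomplete cases are not the longest, and could go the other way if they tend to be stopped early.

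**The case against.** The strongest reply has four parts.

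*Nothing says that anyone is dropped.* This is true. How to score patients with residual LAVAs is the kind of rule that a full protocol or analysis plan holds, and neither is shown. It stands against any claim that the trial will exclude patients. It does not remove the point that the tested variable, as worded, is undefined for patients whom the article expects, and that its power sentence uses another wording.

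*The harm comes mostly from resistant LAVAs, which have no elimination time under either wording.* This is right, and it is why harmonizing on targeted LAVAs is not enough.

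*Spared LAVAs are a matter of anatomy, so randomization balances them in expectation.* This is fair for the example given. It does not help with resistant LAVAs, which the article expects to differ by arm.

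*The article settles the clock.* A reader might infer that energy-delivery time and elapsed time are confused, and that the 50% is supported only for delivery time because its arithmetic is "3 2.5-second pulse trains = 7.5 seconds per ablation site" against at least 30 seconds per RFA lesion. The documents do not support this. The Abstract, the hypothesis sentence and the Discussion all speak of ablation time; the Discussion keeps it apart from procedure length, and Table 3 lists total procedural duration separately. The power paragraph also gives a second reason, more consistent PFA lesions, which applies on either clock. What remains is that the Endpoints sentence should say ablation time too.

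**Conclusion.** The point holds as a matter of definition, and is worth considering before analysis. The hypothesis sentence fixes a variable that is undefined for patients with residual LAVAs, while the power sentence and the Endpoints section use a different finish line that is still undefined for some of them. The power loss is modest under the assumed counts. The possible arm-dependent selection is the larger matter, but its size and direction depend on a rate and a handling rule that the article does not give.

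Two further inferences should be resisted. One is that the sample size is wrong: no SD is given, the inflation to 40 is correct, and nothing contradicts the assumed 50% difference. The other is that the Discussion introduces a rival primary endpoint when it says "the primary study endpoint is elimination of all LAVAs". That is most likely a slip for the procedural endpoint in the Key Findings: "The immediate procedural endpoint in all patients will be total elimination of abnormal electrograms". It needs a corrected phrase and nothing more.

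**What to change.** Use one definition in the Abstract, the Endpoints section and the hypothesis and power sentences: *total ablation time applied to all targeted LAVAs, recorded for every treated patient whether or not elimination is complete*. State that the 50% refers to this time. In the Discussion, call elimination of all LAVAs the immediate procedural endpoint.

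Report the existing secondary endpoint on residual LAVAs directly beside the primary result. Add a sensitivity analysis that ranks patients with residual targeted LAVAs worst and compares the arms by a rank sum test, a method the article already names.

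The cost is wording, one sensitivity analysis, and recording ablation time in patients with incomplete elimination as well. No patients are added and the 40 stay. The small downside is that time spent differs from time needed: a case abandoned early can look fast. The sensitivity analysis is there to show whether that affects the conclusion.

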Therefore, we have designed a randomized pilot study intended to directly compare the safety and efficacy of PFA vs standard RFA using a prespecified procedural endpoint (elimination of abnormal potentials) in patients with ICM and VT. We hypothesize that the time needed to eliminate the abnormal potentials will be shorter with PFA than with RFA. We will use the new focal FARAPOINT PFA catheter that has similar dimensions and handling to the existing RFA catheters.

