## Methods

The ASCEND-VT trial is a single-center, randomized noninferiority pilot study comparing the efficacy and safety of the novel FARAPOINT PFA catheter vs standard RFA catheters during ablation of VT in patients with ICM. The study conforms to the Declaration of Helsinki. It has been approved by the Cleveland Clinic Internal Review Board and the US Food and Drug Administration, which granted an investigational device exception (G220079). The trial is listed in the ClinicalTrials.gov registry (NCT06891456). The study is investigator initiated and represents collaborative research between Cleveland Clinic and Boston Scientific Corporation. It is funded by Boston Scientific Corporation. Given that this is a trial design manuscript, there are no primary data available for sharing.

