## Discussion

The ASCEND-VT pilot trial is the first randomized prospective study designed to assess the procedural efficacy and safety of VT ablation in patients with ICM, using a focal PFA catheter vs standard RFA technology. The primary efficacy metric of ASCEND-VT is intended to directly compare PFA vs RFA with respect to the time that it takes to eliminate abnormal endocardial potentials (specifically, LAVAs) in this population.

This study design was chosen to test the anticipated primary advantage of the PFA technology in this context: its expected ability to achieve the same procedural endpoint as standard ablation but in a more streamlined fashion. If the ASCEND-VT study reveals similar ablation times between PFA and RFA along with comparable safety profiles, then that alone may boost the former technology’s clinical appeal given that the PFA apparatus does not require large volumes of open irrigation. Furthermore, if the ASCEND-VT study reveals a large primary effect size (ie, large difference in ablation times between the 2 study arms), then we may even postulate a trend toward procedural “superiority” of PFA, that is, substantially shorter ablation that can translate into shorter procedural times, which will confer additional benefits on the patients such as shorter exposure to anesthetic agents, less time under positive pressure ventilation, and overall lower procedural complication risk, as previously reported.^39^

With that in mind, we expect most of the other secondary outcome metrics (such as fluid input/balance and total procedural duration) to mirror the primary outcome. In further secondary analyses, the ASCEND-VT study will also compare the numbers of cases where total elimination of LAVAs could not be achieved. As discussed earlier, this endpoint is sometimes unachievable using RFA.^15^^,^^20^ In contrast, interpretation of this finding may be challenging considering the reversible nature of PFA in certain scenarios.^40^

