## Conclusion

The ASCEND-VT pilot study is a single-center, randomized trial designed to assess the procedural efficacy and safety of focal PFA vs standard RFA in patients with VT and ICM. If this study establishes noninferiority of the PFA technology in this regard, this result will inform the design of future multicenter studies powered to look at the overall clinical efficacy of PFA for VT ablation.

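### The trial is declared a noninferiority trial, but its stated null hypothesis, test and sample size are those of a superiority (difference) design, so a non-significant result could not show noninferiority

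*Protocol article*

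**What the plan says.** All references are to the protocol article.

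**Places that declare noninferiority**
- Methods, opening paragraph: the trial is a "single-center, randomized noninferiority pilot study".
- Key Findings, after the abstract, on the time needed to eliminate late abnormal ventricular activity (LAVA): "This will be tested for noninferiority".
- Conclusion, final section: "If this study establishes noninferiority of the PFA technology in this regard", the result will inform larger trials.

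**Places that describe a difference or superiority design**
- Introduction: "We hypothesize that the time needed to eliminate the abnormal potentials will be shorter with PFA than with RFA".
- Statistical analysis and power calculations: the primary null is that total ablation time "will not be different between the 2 study arms". The next sentence fixes the method: "This hypothesis will be tested using a 2-sample" t test.
- Same section: the sample size assumes that the times differ by at least 50%, with 80% power and a significance level of 0.05. This gives 18 per arm, raised to 40 in total for 10% withdrawal. Whether the level is one- or two-sided is not stated.

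**How results would be read.** The Discussion begins one scenario with "If the ASCEND-VT study reveals similar ablation times between PFA and RFA along with comparable safety profiles" and says that this alone could make PFA more attractive, since PFA does not need large volumes of irrigation. A large difference is presented as a further step, which might suggest a trend toward superiority.

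**The concern.** A noninferiority test has a null hypothesis that the new treatment is worse by at least a stated margin. It concludes in the new treatment's favour only when the confidence interval excludes that margin. The test printed here has a null of equality. Rejecting it shows a difference. Failing to reject it shows nothing about how much slower PFA might be.

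The declared framework and the stated test therefore answer different questions. They diverge when the times do not differ significantly, and the Discussion treats similar times as a favourable outcome. If such a result were then described in the terms of the Conclusion, PFA would be called noninferior without control of the risk that it is materially slower. Small samples and noisy timing make a non-significant result more likely, so they would make that misreading more likely too.

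**Working it through.** **1. Comparing the statements**

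| Element | What noninferiority requires | What the article states |
|---|---|---|
| Null hypothesis | PFA slower than RFA by at least a margin | No difference |
| Test | One-sided, shifted by the margin, or the equivalent confidence-bound rule | 2-sample t test of no difference |
| Basis of sample size | Margin, SD and assumed true difference | A difference of at least 50% |
| Study hypothesis | Not materially slower | Shorter with PFA |

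Every element that the statistical section fixes belongs to a difference design. The finding rests on this conflict in the printed text and does not depend on the numbers below.

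**2. The plan's own sample size**

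The withdrawal step reproduces: 36 / (1 − 0.10) = 40. The 18 per arm cannot be reproduced directly, because neither a mean nor an SD is given. It can be solved backwards for the standardized difference d that gives 80% power at level 0.05 with 18 per arm (noncentral t):
- two-sided: d = 0.961, so SD = 0.50 / 0.961 = 0.52 of the RFA mean;
- one-sided: d = 0.846, so SD = 0.50 / 0.846 = 0.59 of the RFA mean.

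This assumes equal SDs in the arms and reads 50% as 50% of the RFA mean.

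**3. What a non-significant result would leave open, at 20 per arm**

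Half-width of the two-sided 95% confidence interval = t(0.975, 38 df) × SD × √(2/20), with t = 2.024:
- SD 0.52: 2.024 × 0.52 × 0.3162 = 0.333;
- SD 0.59: 2.024 × 0.59 × 0.3162 = 0.378.

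An observed difference of exactly zero would be compatible with PFA taking about 33% to 38% longer.

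Now suppose that PFA truly took 25% longer. The noncentrality parameter is 0.25 / (SD × √(2/20)), which is 1.52 for SD 0.52 and 1.34 for SD 0.59. A two-sided test at 0.05 would be non-significant with probability 0.68 and 0.74 respectively.

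**4. What a significant result would show**

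If the two-sided test is significant with shorter PFA times, the upper 95% bound for PFA minus RFA lies below zero, and so below any positive margin. Noninferiority then follows whatever the margin.

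**5. If noninferiority were tested properly**

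Normal approximation, one-sided 0.025, 80% power, true difference zero, SD 0.52: n per arm = 2 × SD² × (1.96 + 0.84)² / margin². This gives:
- 48 per arm for a margin of 30% of the RFA mean;
- 107 per arm for 20%;
- 425 per arm for 10%.

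With 20 per arm and a 30% margin, power (noncentral t) is about 43% for SD 0.52 and 35% for SD 0.59. It is lower for smaller margins. If PFA is truly 50% shorter, 7 to 12 per arm suffice for margins of 30% down to 10% (normal approximation, SD 0.52).

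**The case against.** The strongest defence is that the defect may never matter. The trial expects PFA to be much faster and is sized for a 50% difference. If that holds, the stated test has about 80% power with 18 per arm (two-sided, SD 0.52), and a significant result supports the planned conclusion at any margin. This stands, and it limits the problem to a non-significant result.

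A reader might infer that the plan will report a p value above 0.05 as noninferiority. The article does not say so. The Discussion speaks of similar times without giving a decision rule, similarity could be judged from the estimate and its interval, and the Conclusion is conditional. What can be said is that the misreading is open, because the article prints no other criterion.

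A reader might also make the missing margin the main fault. This is a condensed article, and a margin may be given in a full protocol or analysis plan that is not shown. The point therefore rests on the null, test and sample-size basis that are printed, which an unseen document could not reconcile with the declared design. Nor should the Discussion's remark on clinical noninferiority for recurrence and mortality count as evidence, since it concerns a future multicenter trial.

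Finally, PFA being 25% slower runs against the trial's expectation, and the article expects PFA lesions to be more consistent, so equal SDs are doubtful. The figures illustrate imprecision and do not predict a result. Pilot status lowers the stakes but does not remove the conflict, because the trial has a powered primary test and anticipates a noninferiority conclusion.

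**Conclusion.** The point holds in this form: the article declares noninferiority in its Key Findings and Methods and anticipates that conclusion at the end, while its primary hypothesis, test and sample size are for a difference. The text is wrong as written and needs correcting, because it governs the trial's primary claim.

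The consequence is confined to a non-significant result, which would be inconclusive and could be mistaken for noninferiority. At 20 per arm such a result could leave open PFA times about a third longer than RFA. A true excess of 25% would go undetected in roughly 68% to 74% of trials. These sizes rest on a back-calculated SD of 52% to 59% of the RFA mean, equal in both arms, and on a two-sided 0.05 test.

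**What to change.** **Preferred.** Describe the primary analysis as a two-sided difference (superiority) comparison of the time to eliminate LAVA. Remove the noninferiority wording from the Key Findings, the opening of the Methods and the Conclusion. State that a non-significant result is inconclusive and that the estimated difference will be reported with its 95% confidence interval in every case. This is a change of wording and needs no extra patients. What is given up is the option of presenting a null result as noninferiority.

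**If noninferiority is kept.** Before outcome data are seen:
- prespecify and justify a margin for PFA minus RFA;
- conclude noninferiority only if the upper limit of the two-sided 95% confidence interval is below that margin, and then test superiority, which in that order needs no adjustment of the significance level;
- state the SD assumed and the resulting power.

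This option is not free. With 40 patients, power is low for margins of about 30% of the RFA mean or less if the times are truly equal, and the plan should say so.
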